##### 2.5.2.1. Corrections Victoria Treatment Readiness Questionnaire (CVTRQ)

The Corrections Victoria Treatment Readiness Questionnaire [CVTRQ; (91)] is a self-report measure designed to assess treatment readiness in offenders who have been referred to a cognitive skills program. It comprises 20 items and consists of four scales: (1) Attitudes and motivation, (2) emotional reaction, (3) offending beliefs, and (4) efficacy. Each item has to be answered on a five-point Likert-scale. The CVTRQ shows an acceptable convergent validity, discriminant validity as well as predictive validity (91). To the best of our knowledge, there is no validated German version of the CVTRQ. @myTabu translated the CVTRQ. The translation was checked and translated back into English. Resulting differences due to adaptation were inspected and discussed in terms of item content.

##### 2.5.2.2. Readiness to Change Questionnaire (RCQ)

The Readiness to Change Questionnaire [RCQ; (92)] is a 12-item questionnaire originally designed to identify the stage of change reached by individuals who excessively drink alcohol. The German version [RCQ-D; (93)] was adapted within the project by changing the questions regarding drinking of alcohol in questions regarding the offenses of ISAC and ICCSEM. Responses are made on a five-point Likert-scale. The RCQ-D as well as the RCQ shows good psychometric properties (93). Psychometric properties of the version adapted for ISAC and ICCSEM are not available yet.

##### 2.5.2.3. Optimized Questionnaire for the Measurement of Psychological Reactance (OQMPR)

The Questionnaire for the Measurement of Psychological Reactance [QMPR; (94)] is a questionnaire for the assessment of psychological reactance defined as the theory that people resist attempts to constrain either their thoughts or their behaviors. The Optimized Questionnaire for the Measurement of Psychological Reactance [OQMPR; (95)] is a German variant of the QMPR. The OQMPR consists of 12 statements on a five-point Likert-scale. It has a test-retest-reliability of *rtt* = 0.85 (95).

##### 2.5.2.4. Social Support Questionnaire (F-SozU K-7)

The seven-item short version of the Social Support Questionnaire (F-SozU K-7) is an efficient questionnaire to assess perceived social support (96). Each item comprises a five-point Likert-scale. Internal consistency of the original long version showed Cronbach's α between 0.81 and 0.93 (97).

##### 2.5.2.5. University of California Los Angeles Loneliness Scale (UCLA)

The UCLA Loneliness Scale (98) consists of 20 items in order to assess subjective feelings of loneliness. The German short version (99) consists of 12 items on a four-point Likert-scale. A German study with ISAC and ICCSEM demonstrated a high reliability of α = 0.92 (100).

##### 2.5.2.6. Bumby Molest Scale (BMS)

The Bumby Molest Scale [BMS; (76)] is a self-report questionnaire which assesses cognitive distortion in ISAC [German Version: (101)]. It consists of 38 items on a four-point Likert-scale. The German version shows good construct validity, internal consistency, and test-retest reliability (101).

##### 2.5.2.7. Social Problem-Solving Inventory Revised (SPSI-R)

The Social Problem-Solving Inventory Revised [SPSI-R; (102)] is a self-report questionnaire for the assessment of the five dimensions in the social problem-solving model: (1) positive problem orientation, (2) negative problem orientation, (3) rational problem solving, (4) impulsivity/carelessness style, and (5) avoidance style. The SPSI-R consists of 52 items on a five-point Likert-scale. It shows good psychometric properties for individuals who have sexually offended (72). The validated German version is a short form consisting of 25 items (103).

##### 2.5.2.8. Difficulties in Emotion Regulation Scale—Sub-scale Impulsivity (DERS)

The Difficulties in Emotion Regulation Scale [DERS; (104)] is a self-report questionnaire to assess emotion dysregulation. The sub-scale “impulse control difficulties” is used as outcome measure and comprises five items on a five-point Likert-scale. The German version is used, which shows a good internal consistency, construct and predictive validity (105).

##### 2.5.2.9. Negative Affect Repair Questionnaire (NARQ)

The Negative Affect Repair Questionnaire [NARQ; (106)] is a self-report questionnaire to assess strategies to regulate negative affect in a systematic manner. It consists of 17 items on a five-point Likert-scale and provides a good construct validity. Reliability scores (Cronbach's α) for the three NARQ scales ranged between 0.71 and 0.80 (106).

##### 2.5.2.10. Barratt Impulsiveness Scale-15 (BIS-15)

The Barratt Impulsiveness Scale [BIS; (107)] is a questionnaire developed to assess the personality/behavioral construct of impulsiveness. It consists of 30 items on a four-point Likert-scale. The German short version [BIS-15; (108)] consisting of 15 items is used in the clinical trial. The BIS-15 is an efficient measure of impulsiveness with good internal consistency [α = 0.81; (108)].

##### 2.5.2.11. Coping Using Sex Inventory (CUSI)

The Coping Using Sex Inventory [CUSI; (109)] is a questionnaire to assess the presence of and the degree to which sex was used to deal with problematic situations. It consists of 16 items on a five-point Likert-scale with a satisfying internal consistency (109). The translation was checked and translated back into English by the authors. Resulting differences due to adaptation were inspected and discussed in terms of item content. For another German translation, it has been shown that the CUSI is able to assess therapy-induced changes of ISAC (2).

##### 2.5.2.12. Hypersexual Behavior Inventory-19 (HBI-19)

Sexual preoccupation is assessed by the Hypersexual Behavior Inventory-19 [HBI-19; (110)]. The HBI-19 is a three-factor measure (coping, control, and consequences) developed to assess hypersexual behavior. The instrument consists of 19 items (e.g., “I use sex to forget sorrows of everyday life.”) answered on a scale from 1 (never) to 5 (very often). The maximum score is 95, with higher scores indicating a higher level of sexual preoccupation. The questionnaire was shown to have good reliability (α = 0.90) and validity (110).

##### 2.5.2.13. Questionnaire on Emotional Congruence with Children-Revised (EKK-R)

Emotional congruence with children is assessed by the Questionnaire on Emotional Congruence with Children-Revised [EKK-R; (111)] including three factors (special relationship to children, immaturity, and emotional closeness to children). Twenty items are answered on a four-point scale. The questionnaire demonstrated good reliability (α = 0.80) and validity (111).

##### 2.5.2.14. Specific self-efficacy for modifying Sexual Interest in Children (SSIC)

Specific self-efficacy for modifying sexual interest in children (SSIC) is assessed by the Self-Efficacy for Modifying Sexual Interest in Children Scale [SSIC-Scale; (112)]. Six items on the participant's conviction regarding the ability to change their sexual interest in children (e.g., “I can succeed in reducing my sexual interest in children”) were answered on a scale from 1 (do not agree at all) to 5 (totally agree). The maximum score is 30, with higher scores indicating a higher level of self-efficacy. The instrument was shown to have good reliability (α = 0.87) and validity (112). Four variables that were shown to be related to the SSIC (113, 114) are also assessed: flexibility of sexual interest in children (three items on previous experiences concerning changes in the participant's sexual interest in children), exclusiveness of sexual interest in children (single-item question), motivation to change sexual interest in children (single-item question), and age of onset of sexual interest in children (single-item question).

##### 2.5.2.15. The Explicit Sexual Interest Questionnaire (ESIQ)

The Explicit Sexual Interest Questionnaire [ESIQ; (115)] directly assesses pedophilic interest. It consists of two scales measuring sexual behavior (20 items, e.g., “I enjoyed orally stimulating a man.”) and sexual fantasies (20 items, e.g., “I find it attractive to imagine a little boy sexually stimulating me.”). All items are answered on a scale from 1 (totally disagree) to 5 (totally agree). The reliability of the instrument ranges between 0.86 and 0.97 (115).

##### 2.5.2.16. Outlet Inventory-Revised (SOI-R)

The second measurement for sexual interest in children is the Item 2a of the Sexual Outlet Inventory-Revised [SOI-R; (116)] which assesses the desire for sexual activity involving children on a visual analog scale from 0 (desire is absent) to 100 (I have to act to satisfy the desire). Higher values on the scale indicate a stronger sexual interest in children (116).

#### 2.5.3. Additional Questionnaires

Some questionnaires will be administered additionally but have no direct explanatory power with regard to primary or secondary outcomes. There are no concrete hypotheses regarding secondary or primary outcome. Questionnaires are administered for descriptive purposes, security reasons or to control for possible bias effects (e.g., volunteer-effects).

##### 2.5.3.1. Working Alliance Inventory-Short Revised (WAI-SR)

The WAI-SR (117, 118) measures three dimensions of therapeutic alliance: (a) bond, (b) task, and (c) goal. For the purpose of this study, the original items of the German version (119) were adapted to be suitable for a web-based intervention. The items have to be rated on a five-point Likert-scale ranging from 1 (never) to 5 (always). It was adapted to suit to the online-coach as well as the SO resulting in 16 items. Internal consistency (Cronbach's α) of the original questionnaire ranges from 0.82 to 0.90 (119).

##### 2.5.3.2. Questionnaire of Subjective Therapy Preconditions (SBV-R)

The SBV-R (120) measures the multidimensional construct of therapy and treatment preconditions in offenders. In this study, the only sub-scale used is “pressure of pain.” The pressure of pain is defined as an aversive state in which the person affected recognizes conflicts as lying within him or her (121). The eight items of this sub-scale are rated on a five-point scale. The internal consistency (Cronbach's α) of the sub-scale pressure of pain is 0.75 (120).

##### 2.5.3.3. WHO-5 Well-Being Index (WHO-5)

The WHO-5 (122) is a questionnaire that measures current mental well-being with five items. The items are rated on a six-point Likert-scale ranging from 0 (at no time) to 5 (all of the time). The WHO-5 has shown good validity in measuring subjective well-being in clinical studies (123).

##### 2.5.3.4. Questionnaire for Acceptance of Technology (ATQ)

To assess acceptance of technology and its predictors within the framework of this project, a questionnaire for acceptance of technology (ATQ) was designed. The ATQ is based on the Unified Theory of Acceptance and Use of Technology (UTAUT) which defines acceptance as behavioral intention of using a certain technology. According to the model, predictors of this intention are performance expectancy, effort expectancy, and social influence. Predictors of actual technology usage are facilitating conditions, such as organizational or technical preconditions (124). The ATQ comprises items which measure acceptance and the previously named predictors from the UTAUT model as well as additional items concerning following extended predictors: internet anxiety, attitude toward using technology, planning, and importance of monetary compensation. The items of the ATQ were either self-constructed or derived from questionnaires used in former studies and adapted if conceptually required (125–127). Internal consistency (Cronbach's α) of the original scale ranges from 0.68 to 0.92. To control for effects of compensation, two items concerning importance of study compensation were self-constructed.

##### 2.5.3.5. Mood and Risk Questionnaire (MRQ)

The Mood and Risk Questionnaire (MRQ) was developed to assess acute changes with regard to emotional well-being and thoughts associated with potential re-offenses as a direct cause of working on sessions within the web-based intervention. It consists of ten self-developed items, of which six are asking about thoughts and behaviors associated with potential re-offenses and four asking about the psychological and emotional state of the participant. The MRQ is provided before and after each session.

##### 2.5.3.6. Questionnaire of Non-Participation (QNP)

The Questionnaire of Non-Participation (QNP) was developed to assess reasons for not taking part in the study. It comprises eleven items on a six-point Likert-scale. Items are e.g., “I will not take part in the study because I do not need any further help.” or “I will not take part in the study because I am afraid of negative consequences if my SO gets additional information about me.” The QNP will only be administered if a potential participant will not take part in the study but has given informed consent to fill out this questionnaire.

### 2.6. Procedure

The clinical trial starts on January 01, 2021 and ends on December 31, 2022. All potential participants are screened by their SO based on inclusion criteria and the SO hands out written information on the trial. If the potential participant is generally interested in participating, an individual meeting with an independent research assistant will take place at the supervision office. During this meeting, the research assistant provides detailed information about the goals and procedure of the trial, data security and advantages or disadvantages of taking part in the trial. If the potential participant is further interested to take part, he or she will receive an information letter, the informed consent, an intervention agreement, and a letter releasing the SO from the confidentiality obligation. In the intervention agreement, the participant agrees not to commit offenses during the participation and is informed that any violation will lead to exclusion. Furthermore, the research assistant performs the pre-intervention assessments (see Supplementary Table 1). If a potential participant does not want to take part in the trial, he or she will be asked for informed consent in filling out one questionnaire (QNP) and to allow to fill out the SSQ-CF checklist by the research assistant as well as the SSQ-SO by the SO. Further, the potential participant is asked for allowance to assess his or her officially registered re-offenses in a 5-years follow up in order to be able to control for a potential volunteer-effect. After obtaining the written informed consent, the intervention agreement, and the release from confidentiality, the participant is randomly allocated to the experimental or the control condition. The username as well as the initial password is delivered by post to the SO, who will give it to the participant. After the first log-in, the participant has to change the initial password due to security reasons. After changing the initial password, the participant has to go through an introduction, which explains the usage of the intervention website, before he or she can start with the first online module. The procedure for the placebo condition is the same as for the experimental condition, only the provided online contents differ. In both the placebo and the intervention condition, the provided content is divided into six online modules. Each module is further divided into four sessions. Each session has a duration of about 60 min and the participant is advised to finish one session per week. Consequently, the intervention as well as placebo consists of 24 sessions which can be completed in 24 weeks. The participant will be reminded by in-app messages or by the SO if he or she is late in finishing the next session. During both online conditions, data of primary outcome (IoD) is assessed at 7 measurement time-points. Except questionnaires which are filled out at clearing up all questionnaires are provided online within the web-based app. This ensures that the questionnaires are filled in at the predefined measurement time-points. Five years after the last patient out, re-offenses are assessed by officially documented re-offenses (see Supplementary Table 1 for an overview on measurement time-points).

### 2.7. Randomization

The trial comprises two parallel groups (web-based intervention group and web-based placebo group). Subjects are randomly allocated to treatment using an allocation ratio of 1:1. The randomization lists are centrally generated using a computerized system (SecuTrial® www.secutrial.com, a for-profit organization) stratified by the offense type (§§176, 176a, 176b StGB vs. §184b StGB), type of CS (§§56, 57 StGB vs. §§68 ff StGB), treatment in addition to CSaU (external psycho-therapeutic and/or medical treatment vs. no treatment), and risk to re-offend at baseline [assessed with the modified Static-99 (43) for ICCSEM and the Static-99 (42) for ISAC]. At screening, each subject receives the next consecutive screening number. At randomization, each subject eligible for study participation receives the next consecutive randomization number according to his stratum from a block of randomization numbers (block size: 4).

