##### 2.2.3.4. Sample Specifications Questionnaire based on the Court File (SSQ-CF)

The SSQ-CF is a checklist for coding court files. Information from the court files is coded with the SSQ-CF by the study investigators to determine whether the participant meets the study inclusion criteria and to be able to fill out the Static-99 (42) (only CSOs) or modified Static-99 (43) (only ICCSEM). This includes information on the probation period, index offense, and former offenses. In case that items of the SSQ-CF cannot be filled out adequately by utilizing court files, the participants will be interviewed directly.

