### 2.8. Blinding

Due to security reasons, blinding of SOs and supporting coaches is not possible. Nevertheless, participants, members of the data safety monitoring board (DSMB), and data analysts (observer) are blinded until the end of the data analysis. The DSMB is independent from the sponsor.

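### A single published block size of 4, with supervision officers and coaches unblinded, makes one third of allocations certain to anyone who knows a stratum's earlier ones. Randomly varying block sizes would be a cheap improvement.

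*Protocol article*

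**What the plan says.** All references are to the protocol article.

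- **Section 2.7 (Randomization).** "Subjects are randomly allocated to treatment using an allocation ratio of 1:1". "The randomization lists are centrally generated using a computerized system". Each eligible person "receives the next consecutive randomization number according to his stratum", taken "from a block of randomization numbers (block size: 4"). The four stratification factors are offense type, type of community supervision, treatment beyond usual supervision, and baseline risk on the Static-99 or its modified form. Site and officer are not among them.
- **Section 2.8 (Blinding).** "blinding of SOs and supporting coaches is not possible". Participants, the monitoring board and data analysts are listed as blinded. Research assistants and the investigators who code files are not mentioned either way.
- **Section 2.6 (Procedure).** "All potential participants are screened by their SO based on inclusion criteria", and the officers hand out the trial information. An independent research assistant then informs the candidate and does the baseline assessments. Allocation comes after written consent.
- **Section 2.2.3.4 (SSQ-CF).** "Information from the court files is coded with the SSQ-CF by the study investigators", which supplies the Static-99 and so one of the stratification factors.

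Neither a varying block size nor any other measure against prediction is stated.

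**The concern.** When the people who refer candidates learn the arms, the main safeguard left at that step is that the next allocation cannot be foreseen. Central generation protects the list itself. It does not stop someone inferring the next entry from past entries when the block length is short, fixed and published.

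Someone who could foresee the next arm might, without any ill intent, change when a candidate is put forward, how strongly participation is encouraged, or how a borderline file is coded into a stratum. That would introduce selection that randomization is meant to exclude. The steps exposed here are mainly referral by the officer and coding of the stratum, because consent precedes allocation.

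**Working it through.** **The plan's own figures.** The article gives no figure for predictability. Its only computed design figure is power, which reproduces: 0.27 × √(214/2) − 1.96 = 0.833, giving 79.8% against the stated 80%. Completers also reproduce: 582 × (1 − 0.264) = 428. The present point does not depend on the power. It uses only the planned 582 randomized (section 2.10), the 1:1 ratio and the block size of 4 (section 2.7).

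**1. Certain allocations in a complete block of 4.** There are six equally likely orders: AABB, ABAB, ABBA, BBAA, BABA, BAAB. An allocation is certain once one arm has been used twice.
- Position 4 is always certain.
- Position 3 is certain only in AABB and BBAA, so with probability 2/6 = 1/3.
- Share certain = (1 + 1/3)/4 = 33.3%. If every block were filled, that is 582/3 = 194 allocations.

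**2. Best guess in a complete block of 4.** The probability of being right is 1/2 at position 1, 2/3 at position 2, 1/3 + (2/3)(1/2) = 2/3 at position 3, and 1 at position 4. The sum is 2.833, and 2.833/4 = 70.8%, against 50% by chance.

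**3. Unfinished last blocks.** Relative to one third of its participants, a stratum loses 0, 1/3, 2/3 or 2/3 certain allocations when 0, 1, 2 or 3 people remain in its last block. The average loss is 5/12 per stratum if remainders are equally likely. With K strata the share is 1/3 − (5/12)K/582. Three of the four factors have two levels (8 cells). The number of risk levels is not stated, so K is an assumption.

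| Assumed risk levels | K | Share certain | Of 582 |
|---|---|---|---|
| 2 | 16 | 32.2% | 187 |
| 3 | 24 | 31.6% | 184 |
| 4 | 32 | 31.0% | 181 |
| 5 | 40 | 30.5% | 177 |

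Simulated stratum counts, even and uneven, give the same 30.5–32.2%.

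**4. What a partial view yields.** Suppose an observer sees each earlier allocation in the stratum with probability q and, generously, is also told the position in the block. Certainty requires having seen both members of the arm that is used up, so the share is (q² + q²/3)/4 = q²/3. The values of q are assumptions.

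| q | Share certain |
|---|---|
| 5% | 0.08% |
| 10% | 0.33% |
| 25% | 2.1% |
| 50% | 8.3% |
| 100% | 33.3% |

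**5. Randomly varying sizes.** The observer is assumed to know every earlier allocation in the stratum and the set of possible sizes, but not their order. In each simulated sequence the probability of the next arm was updated over all block states compatible with the history, and an allocation counted as certain when that probability was 0 or 1.

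| Scheme (36 per stratum) | Certain | Best guess right |
|---|---|---|
| 4 only (control) | 33.3% | 70.8% |
| 4 and 6 mixed | 5.7% | 68.8% |
| 4, 6 and 8 mixed | 2.4% | 67.5% |

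For the 4/6/8 scheme, strata of 12 to 72 people give 2.3–2.5% certain and 66.5–67.8% guessed correctly.

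**The case against.** The strongest reply is that the article shows nobody with both the knowledge and the opportunity. Lists are central and strata run across the whole trial, so an officer sees only a scattering of each sequence, and step 4 shows how quickly the one-third figure shrinks. Coaches are unblinded but have no described part in screening, consent or stratum coding. The person who informs candidates is an independent research assistant, and allocation follows consent. With 582 people over possibly 16 or more strata, short blocks are a defensible way to keep balance. The models also limit bias from measured selection: the Index of Desistance model adjusts for its baseline value and three of the four factors, and the re-offense model for all four.

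Most of this stands, and it sets the weight of the point. It does not explain why the size should be fixed and disclosed when officers at the referral step cannot be blinded.

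A reader might infer that officers can in practice foresee a third of allocations, or that research assistants and investigators are unblinded and see the running allocations. The documents support neither. The one third is conditional on knowing the stratum's whole history. Section 2.8 is silent on assistants and investigators, and system access rights are the kind of detail a condensed article leaves to the full protocol. Nor does the text support a claim that either primary outcome will be biased by a stated amount.

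**Conclusion.** The point holds as a low-severity design improvement. The rule in section 2.7 makes 33.3% of allocations certain in complete blocks, about 30–32% with unfinished ones, and allows about 71% correct guesses. Both figures apply only to an observer who knows all earlier allocations in the stratum. The 30–32% also assumes 16 to 40 strata. A single officer will rarely be such an observer. Who can see cumulative allocations is not stated, so the real frequency of prediction, and any resulting bias, cannot be computed.

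A reader might also conclude that varying the blocks abolishes the problem at no cost. It does not. It nearly eliminates certain allocations, but a well-informed guess would still be right about 67–68% of the time, and there is a small price in balance.

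**What to change.** For lists or blocks not yet used, replace the parenthetical block size in section 2.7 with wording such as: permuted blocks of randomly varying size within stratum, with the sizes and their sequence withheld from supervision officers, coaches, research assistants and the investigators who code the strata. Sizes of 4, 6 and 8 are one workable set, to be recorded in a restricted document held by whoever generates the lists.

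The cost is regenerating the unused lists and a slightly larger possible imbalance within small strata: an unfinished block of 8 can leave the arms up to 4 apart, against 2 for a block of 4. Sample size, analysis models and participant burden are unchanged. Blocks already in use need not be touched.
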